## Abstract

**Background:**

Patients ≥ 70 years with small, low-risk breast cancer who are operated but not irradiated how local relapse rates around 4% after 4 years. With adjuvant whole breast radiotherapy (WBRT) the local relapse rate drops to 1% after 4 years under Tamoxifen. It has been demonstrated that the efficacy of radiotherapy of the tumor bed only in a selected group can be non-inferior to WBRT.

**Methods/Design:**

This prospective, multicentric single arm phase II study is based on the protocol of the international TARGIT-A study. The TARGIT-E study should confirm the efficacy of a single dose of intraoperative radiotherapy (IORT) in a well selected group of elderly patients with small breast cancer and absence of risk factors. Patients will receive IORT (20 Gy with Intrabeam system/Carl Zeiss) during breast conserving surgery. In presence of risk factors postoperative WBRT will be added to complete the radiotherapeutic treatment according to international guidelines. Endpoints are the local relapse rate (within 2 cm of the tumor bed), ipsilateral in breast relapse, cancer-specific and overall survival and contralateral breast cancer as well as documentation of quality of life and cosmetic outcome.

The expected local relapse rates are 0.5/1/1.5% after 2.5/5/7.5 years, respectively. Discontinuation of the trial is scheduled if rates of local relapse rates rise to 3/4/6% after 2.5/5/7.5 years. Power calculations result in 540 patients with a calculated dropout rate of 20% and loss to follow-up of 20%, an alpha of 0.01 and a beta 0.05. There will be a pre- and a post-pathology stratum (n = 270 each).

**Discussion:**

It is a pragmatic trial in which each participating centre has the option to modify entry criteria and criteria for WBRT according to this core protocol after consultation with the steering committee and local ethics committee (e.g. size, free margins). Only centers with access to the Intrabeam system (Carl Zeiss) can recruit patients into the trial.

Its aim is to confirm the efficacy and toxicity of IORT in a well selected collective of elderly patients with breast cancer.

**Trail registration:**

NCT01299987

## Background

Randomized studies provide evidence that concerning the overall survival, breast conserving surgery (BCS) combined with postoperative radiotherapy is equally effective to modified radical mastectomy
[1-3]. Postoperative radiation significantly decreases the local relapse rate
[1,2] in comparison to BCS alone
[3]. The recent metaanalysis of the Early Breast Cancer Trialists Collaborative Group (EBCTCG
[3]) shows that the avoidance of 4 local relapses after 5 years can prevent one death in 15 years (4 to 1 rule).

Several studies have demonstrated in the past that complete omission of radiotherapy failed in terms of local tumor control. Fyles et al.
[4] showed local relapse rates of 8% within a low risk group of patients with tumors of pathological stage T1/T2 and >50 years of age treated with BCS and antihormonal treatment (AHT). By adding postoperative whole breast radiation (WBRT) the rate of local relapse was reduced to 1% after 5 years. This effect was also seen in elderly patients with small tumors. Hughes et al.
[5] observed low local relapse rates of 4% for patients treated with AHT only after BCS vs. 1% for patients with additional WBRT after 4 years, evaluating a low-risk group of patients with tumors < 2 cm and > 70 years of age. Apparently, all patients benefit from postoperative WBRT. However, due to the fact that up to 90% of all local relapses after breast conserving therapy are localized very close to the primary tumor, it might be possible to treat a selected group of patients with a relatively low risk of local recurrence with tumor bed irradiation only. Polgar et al.
[6] provided evidence of the non-inferiority of accelerated partial breast irradiation (APBI) in comparison to WBRT in a small randomized trial. Very recently the TARGIT-A data
[7] reported a non-inferior efficacy of tumor bed irradiation with single dose intraoperative radiation (Intrabeam system, Carl Zeiss Oberkochen) compared to WBRT regarding local relapse.

By using the Intrabeam system, the intraoperative radiotherapy (IORT) can be given during surgery with protection of the surrounding tissue while applying a biologically highly effective dose to the tissue adjacent to the tumor. Advantages of IORT are its high precision regarding beam application, possibility of protection of the skin and the prevention of tumor cell proliferation during the time interval between surgery and adjuvant WBRT and during fractionated WBRT. By manually positioning of the applicator in the tumor bed geographic miss is excluded and radiation exposure of risk structures like the heart and lung can be avoided. Therefore, it is possible to give a single high dose to the target while minimizing relevant side effects.

## Methods/Design

### Study design

This prospective, international, multicentric single arm phase II study is based on the protocol of the international TARGIT-A study. The TARGIT-E study should confirm the efficacy of a single dose of intraoperative radiotherapy (IORT) in a well selected group of elderly patients with small breast cancer and absence of risk factors. Patients treated with breast conserving surgery and IORT will only be followed by WBRT when risk factors are present. There will be a pre- and a post-pathology stratum.

### Pre-pathology stratum

Patients will enter the trial after careful clinical examination according to the inclusion criteria. Patients who are planned to have IORT at the time of primary surgery will be addressed in this stratum after giving consent prior to the planned surgery. Additional post-operative WBRT is given only when risk factors are present. This stratum will be closed after 270 patients are treated.

### Post-pathology stratum

Patients will be recruited for entry to the trial only once the pathological characteristics of the tumor have been reported. These patients will have local surgery as per usual practice and if the patient and the tumor fit in the criteria defined in the protocol and the investigator’s treatment policy, she will be asked for consent to enter the trial and if given she will have further surgery at which the wound is opened, the probe inserted and the radiation dose given. This stratum of patients addresses a much more explanatory question as their entry to the trial will be strictly defined on pathological grounds. However, the disadvantage for these patients is that they must have a second surgery. Including these patients will allow an assessment of the local control obtained in very good prognosis patients.

This strategy also allows for the entry of patients who have already received surgery at an outlying centre. The post-pathology stratum will recruit 270 patients.

### Trial design

The treatment schedule of this single arm phase II study is shown in the study flow chart (Figure
1).

**Figure 1 F1:**
[figure not shown]
**Systemic therapy according consensus giudelines (St. Gallen).** EIC – extensive intraductal component, WBRT – whole breast radiotherapy, SNB – sentinel node-biopsy, BCS – breast conserving surgery L1 – lymphangio invasion *modifications according to local protocols and national guidelines; **with reference to national guidelines a re-resection should be performed in presence of positive resection margins (e.g. <1cm in Germany).

### Recruiting

first patient: January 2011

last patient: December 2015

follow-up: 10 years

### Study objectives

The objective of this single armed phase II study is to investigate the efficacy of a single intraoperative radiotherapy treatment within elderly low risk patients (≥ 70 years, cT1 and small cT2, cN0, cM0, invasive-ductal) which is followed by WBRT only when risk factors are present. For both primary and secondary efficacy measures descriptive statistics will be calculated and Kaplan-Meier plots will be generated. There will be a separate subgroup analysis of the pre- and post-pathology strata performed according to primary and secondary endpoints.

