### Secondary objectives

The secondary objectives are ipsi- or contralateral breast cancer, cancer specific and overall survival, cosmetic outcome and quality of life.

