### Inclusion criteria

histologically verified invasive-ductal breast cancer

cT1 or small cT2 (≤ 3.5 cm) cN0 cM0

≥ 70 years of age

informed consent

compliance

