#### Follow up

Follow-up visits will be scheduled after 6 weeks, 4.5 months, 6 months and annually after radiotherapy. Photographic documentation and assessment of quality of life will be performed at follow-up visits as well as documentation of general condition, weight, new symptoms according to CTC and LENT SOMA score. Furthermore mammography and ultrasound of the breast will be performed according to international guidelines.

Acute side effects in patients, who received postoperative WBRT, will be documented by the CTC score.

The follow-up and documentation of patient specific data will end after 10 years after therapy.

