## Assessment of efficacy parameters

### Relapse

At each follow-up visit there will be a clinical examination to assess local relapse (within 2 cm around the tumor bed) by palpation. Relapses more than 2 cm distant from the tumor bed will count as an ipsilateral relapse. Therefore mammography and ultrasound of the breast will be performed according to international guidelines.

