### Serious adverse events (SAE)

Serious adverse events (SAEs) are defined as any event that is fatal, life threatening, causes or prolongs hospitalization; causes disability or incapacity or requires medical intervention to prevent permanent impairment or damage, or any grade 4 toxicity.

In case of death an autopsy should be done to clarify the cause of death.

Regarding the comorbidity of elderly patients only radiation related SAEs (rrSAEs) grade 4 and 5 including date and on-/offset should be reported. Furthermore rrSAEs requiring therapy should be documented (e.g. antibiotics, aspiration).

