### Description of the primary efficacy analysis and population

A single group of patients is studied. The proportion of patients who respond to treatment (i.e. local relapse free) will be used to estimate the true response rate with a 95% confidence interval. A response rate of 99.5%/99%/98.5% at 2.5/5/7.5 years is anticipated. A response rate of 97%/96%/94% is considered to be the minimum level.

Therefore, efficacy analyses will be performed at two stages.

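### Kaplan-Meier is the only time-to-event method named for ipsilateral relapse, contralateral cancer and cancer death; read as actual risk in women of 70 or more, it runs somewhat too high

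*Protocol article*

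**What the plan says.** The method is in the protocol article under Study objectives: "For both primary and secondary efficacy measures descriptive statistics will be calculated and Kaplan-Meier plots will be generated". The measures it covers are listed under Secondary objectives: "The secondary objectives are ipsi- or contralateral breast cancer, cancer specific and overall survival, cosmetic outcome and quality of life".

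The section on relapse assessment defines the ipsilateral event by distance alone: "Relapses more than 2 cm distant from the tumor bed will count as an ipsilateral relapse". Death is not part of it, and nothing in the article adds death to the contralateral or cancer-specific endpoints.

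The inclusion criteria require "≥ 70 years of age", and on duration the Follow up section says: "The follow-up and documentation of patient specific data will end after 10 years after therapy". The section on serious adverse events restricts reporting because of illness in this age group ("Regarding the comorbidity of elderly patients only radiation related SAEs (rrSAEs) grade 4 and 5") and wants cause of death established: "In case of death an autopsy should be done to clarify the cause of death".

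The primary endpoint has its own estimator. The proportion free of local relapse "will be used to estimate the true response rate with a 95% confidence interval", and the interim rules are counts of relapses (more than 5, more than 8).

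**The concern.** A woman who dies of another cause can no longer have an ipsilateral relapse, develop a contralateral cancer or die of breast cancer. Kaplan-Meier treats her as censored, that is, as if she could still have the event later at the same rate as the women who remain. One minus Kaplan-Meier then describes a setting in which nobody dies of anything else. As a description of a hazard-based, net quantity it is legitimate. As the share of patients who will have the event within 10 years it is too high, and the gap widens as deaths from other causes accumulate.

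The entry age, the length of follow-up and the article's own remark on comorbidity make such deaths likely to matter. The study has one arm, so these secondary rates will be reported and read as absolute risks, overall and in the separate analyses of the pre- and post-pathology strata. What is at stake is the accuracy of those reported risks.

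**Working it through.** The article gives no figure on this point to reproduce: it states no expected rate for the three endpoints and no other-cause mortality. Direction and size can still be worked out.

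**Inputs**
- Follow-up of 10 years and age 70 or more: from the article.
- Other-cause death hazard *d*: assumed 0.03 to 0.06 per year. This means 1 − exp(−0.3) = 26% to 1 − exp(−0.6) = 45% dead of other causes by year 10 if nothing else intervened.
- Event hazard *h*: assumed. One case is 0.005 per year. The other gives a 10-year Kaplan-Meier risk of 2%, which is the article's anticipated local relapse of 0.5/1/1.5% at 2.5/5/7.5 years continued in a straight line. It is borrowed only as an order of magnitude, because it belongs to the primary endpoint.
- Constant, independent hazards: assumed.

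**Formulas**
- One minus Kaplan-Meier: 1 − exp(−*ht*)
- Cumulative incidence: *h*/(*h*+*d*) × (1 − exp(−(*h*+*d*)*t*))

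**Direction.** Whenever *d* > 0 the first exceeds the second. This does not depend on the values chosen.

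**Relative size.** For small *h* the ratio is close to *dt*/(1 − exp(−*dt*)):

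| Time | *d* = 0.03 | *d* = 0.06 |
|---|---|---|
| 5 years | 1.08 | 1.16 |
| 7.5 years | 1.12 | 1.24 |
| 10 years | 1.16 | 1.33 |

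**Absolute size at 10 years, *h* = 0.005**
- Kaplan-Meier: 1 − exp(−0.05) = 4.88%
- Cumulative incidence, *d* = 0.03: 0.005/0.035 × (1 − exp(−0.35)) = 4.22%; excess 0.66 points
- Cumulative incidence, *d* = 0.06: 0.005/0.065 × (1 − exp(−0.65)) = 3.68%; excess 1.20 points

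**Absolute size at 10 years, Kaplan-Meier risk 2%** (*h* = −ln(0.98)/10 = 0.00202)
- *d* = 0.03: 0.00202/0.03202 × (1 − exp(−0.3202)) = 1.73%; excess 0.27 points
- *d* = 0.06: 0.00202/0.06202 × (1 − exp(−0.6202)) = 1.51%; excess 0.49 points

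**Wider range.** If anything from 10% to 50% die of other causes by year 10, the ratio runs from 1.05 to 1.39. The excess is then 0.10-0.56 points for a Kaplan-Meier risk of 2%, 0.20-1.11 for 4%, and 0.30-1.66 for 6%.

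**The case against.** The strongest reply is that one general sentence about plots is being read as an estimator specification. It sits beside a promise of descriptive statistics, gives no censoring rule, and taken literally also covers cosmetic outcome and quality of life. A condensed article may leave competing events to the full protocol or analysis plan. Part of this stands: the censoring is an inference. But the sentence names a method and applies it to the secondary measures, so the point is the suitability of a stated choice and not a missing detail.

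Second, censoring other-cause deaths is a recognised way to describe the effect of a local treatment net of other mortality, and cancer-specific survival is conventionally shown this way. For relapse the excess makes the treatment look worse, not better. This also stands, and it is why Kaplan-Meier should be shown alongside and not removed. It does not supply the actual risk.

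Third, the excess is small beside sampling error. With 540 patients and no losses, a 4.9% estimate has a 95% half-width of 1.96 × √(0.049 × 0.951/540) = 1.8 points, and 2.6 points in a stratum of 270. That is fair. However, sampling error has no fixed direction, whereas this excess always points the same way.

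Two stronger readings are tempting and are not supported:
- A reader might infer that, in a single-arm study, these rates are the whole result. They are not. The main result is the primary proportion with its confidence interval, judged by relapse counts, and no threshold or sample size uses a secondary Kaplan-Meier estimate.
- A reader might add mastectomy after a relapse as a further competing event. The article does not say how relapses are managed, so it gives no basis for this.

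**Conclusion.** The point holds as a matter of reporting accuracy for three secondary endpoints. The direction is certain once other-cause deaths are censored and the curve is read as actual risk. The size rests on assumed mortality: at 3-6% per year with constant hazards, the 10-year excess is about 0.7-1.2 points on a Kaplan-Meier risk of 4.9% and about 0.3-0.5 points on a risk near 2%, or 16-33% in relative terms. The underlying cause-specific hazard is not biased by this censoring.

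The estimate of the primary endpoint as a proportion, the stopping rules and overall survival are untouched. A Kaplan-Meier plot of local relapse, which the same sentence also covers, calls for the same care in reading but does not drive the decision. This is a cheap improvement, not a flaw in the design.

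**What to change.** Change the sentence under Study objectives so that:
- ipsilateral relapse, contralateral breast cancer and breast-cancer death are reported as cumulative incidence (Aalen-Johansen), with death from other causes as a competing event;
- Kaplan-Meier curves for these three are shown alongside, labelled as net of other mortality, for comparison with published Kaplan-Meier rates;
- overall survival stays with Kaplan-Meier alone.

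The sentence should also say what counts as the competing death: any death before the event for the two tumour endpoints, and any death not due to breast cancer for the third.

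The cost is one revised sentence and a standard routine. Date and cause of death are already needed for overall and cancer-specific survival, so no new data, patients or changes to the stopping rules follow. The downside is slightly more analysis, and a headline figure that compares less directly with published Kaplan-Meier rates, which the second curve largely offsets.

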### Primary objectives

The primary objective is the rate of local relapse (within 2 cm around the tumor bed).

### Secondary objectives

The secondary objectives are ipsi- or contralateral breast cancer, cancer specific and overall survival, cosmetic outcome and quality of life.

## Patient selection

### Population

Elderly patients (≥ 70 years) with histologically verified unifocal (mammography, ultrasound), ductal-invasive, small (≤ 3.5 cm) breast cancer without clinical signs of lymph node involvement or distant metastases.

### Inclusion criteria

histologically verified invasive-ductal breast cancer

cT1 or small cT2 (≤ 3.5 cm) cN0 cM0

≥ 70 years of age

informed consent

compliance

### Exclusion criteria

extensive intraductal component (EIC)

multifocality/-centricity (mammography, breast ultrasound)

lymph vessel invasion (L1)

clinical signs of distant metastases or clinically suspicious lymph nodes

other histology

< 70 years

missing informed consent or non-compliance

bilateral breast cancer at the time of diagnosis

known BCRA1/2 gene mutations (genetic testing not required)

any exclusion criterion in the local centre’s treatment policy

positive resection margins (regarding the post-pathology arm)

## Treatment planning and dose prescription

### Radiologic diagnostics

All patients with primary breast cancer receive standardized staging.

Clinical examination, particularly breast and axilla palpation

Mammography and/or ultrasonography of the breast and histological verification of breast cancer

Breast magnetic resonance imaging is not required

### Surgery

All patients will have local excision of the primary tumor following appropriate clinical work-up. Surgery will be performed according to usual local practice with a complete excision of the tumor. The aim of the local excision should be to achieve a free margin of at least 10 mm whilst maintaining a good cosmetic outcome. The final histological margin should be at least 1 mm clear of all invasive and at least 2 mm for in-situ disease, otherwise a re-resection is recommended (may be modified according to local practice). For superficial tumors an ellipse of overlying skin should be excised to avoid overdosing of the skin. The depth of resection will depend on the position of the tumor within the breast and the size of the breast, but in many instances will extend to the pectoral fascia. In all patients, but especially in those women with non-palpable tumors with mammographic correlate in whom preoperative wire localization has been performed, the specimen should be well orientated with sutures or clips according to local protocols and x-rayed intraoperatively. The specimen x-ray should be examined in theatre to ensure complete excision of the lesion and to help with the assessment of adequacy of the margins. Further tissue should be taken (and marked) from a margin if the x-ray abnormality extends near the margin. It is recommended that intraoperative evaluation of the resection margin is performed by fast frozen sections by the pathologist. A standard sentinel node biopsy must be performed in all patients. Wound closure must be performed meticulously (air and water-tight) and sutures (if non-absorbable), should remain in place for 5–7 days.

### Radiotherapy—IORT dose prescription and delivery

The surgeon and radiation oncologist should choose the largest possible suitable applicator in order to ensure that the highest possible dose is delivered to the tumor bed tissue.

A dose of 20 Gy at the surface of the applicator (in water) is prescribed by the radiation oncologist and delivered to the breast tissue. This takes approximately 20–50 minutes, depending on the size of the applicator.

To minimize radiation induced side effects at the applicator surface and the skin, the distance should be more than 5 mm.

During the radiation treatment, the anesthesiologist, surgeon, radiation oncologist and physicist may remain in the room when necessary. To avoid unnecessary exposure, we recommend that as many people as possible leave the operating theatre, and those remaining either wear a leaded apron or remain behind a shielded screen.

### Conventional radiotherapy (WBRT)

If the final histopathological report provides evidence of risk factors as per local protocol (e.g. EIC, L1, mulitfocality/-centricitiy, larger diameter, other histology or too small free resection margins), a conventional postoperative percutaneous radiotherapeutic treatment with WBRT with 46 Gy will be added in 2 Gy per fraction. WBRT with 50 Gy will be performed in pN1 and WBRT including irradiation of the lymphatic drainage areas with 50 Gy in ≥pN2 situations. A delay of at least 5 weeks is required between IORT and initiation of WBRT. A delay of at least 14 days (21 days recommended) is required between chemotherapy and initiation of WBRT.

### Adjuvant treatment

Adjuvant systemic treatment will be performed according to international guidelines.

